**Figure 1 F1:**
[figure not shown]
Diagram of the timing of the intervention in the SEPREVEN stepped-wedge cluster randomised controlled trial. The trial lasts 20 months (M) per participating unit. Each randomization cluster (C) C1, C2 and C3 comprises 4 units. Intervention is implemented within each randomization cluster following a random sequence. The gray cells represent the (pre-educational) *control* periods, blue cells a 4-months *transition* phase and orange cells the (post-educational) *intervention* periods. The transition phase allows for the time to integrate the program into the units. During this *transition* period the unit is not in a *control* or *intervention* phase and does not contribute to primary endpoint analysis.

Sample selection: Study population and setting

Patient eligibility criteria

Inclusion criteria: All patients will be included as follows:

-In hospital during the 20-month study period between November 23, 2015 and November 2, 2017 (inclusion start dates varying by unit) in one of the 12 participating units,-Corrected GA ≤ 42 weeks (≤42 weeks + 6 days) at the time of admission,-Hospitalization period is longer than 2 calendar days,-Parents have been informed and will not oppose the use of their newborn's data.

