### Randomization and allocation concealment

2.4

Randomization will be performed at the unit-level (no randomization oat the patient level). Before the trial starts, the units will be randomized to one of the 3 sequences (4 units/cluster, see Fig. 1) by use of a computer-generated list, without pre-specified characteristics. Each cluster will receive the intervention at different times: therefore, the total duration of the 3 periods will not be the same for the 12 units. Time blocks of 4 months will be considered, including the individual control and intervention periods as well as the transient phase.

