#### Sample size and power calculation

2.8.1

The primary endpoint is the rate of AEs/1000 patient-days (hospitalization days). Analysis of available data from the literature as well as our own unpublished routine data allowed for anticipating an average basal value of 60 AEs/1000 patient-days in the absence of any intervention. The calculation of the required sample size was based on the Poisson distribution to compare control and intervention AE rates. To do so, calculations were performed according to Hemming and Girling,^[49]^ derived from the initial approach by Hussey and Hughes,^[50]^ to take into account the effect of the stepped wedge (or design effect) study specification on the sample size calculation.

Considering a total number of 12 units divided into 3 randomization clusters over 5 study periods, a 5% two-tailed alpha risk and an intraclass correlation coefficient ranging from 0.01 to 0.1, we will need to include 15 patients per unit per month (i.e., 15 × 4 = 60 patients per cluster per 4-month evaluation period), for a total of 15 × 20 × 12 = 3600 patients over the study period, a cumulative 61,200 to 72,000 patient-days corresponding to an expected mean hospitalization length from 17 to 20 days) to show, with a power of 80%, a minimum relative reduction of 17% in rates of AEs (i.e., a decrease from 60 [control] to 50 [intervention] AEs/1000 patient-days).

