#### Statistical analysis

2.8.2

Stepped-wedge cluster trials present a number of challenges related to intra-cluster correlation, the correlation between data repeated over time, and the need to monitor underlying temporal trends.^[47]^ Accordingly, the analysis of the primary endpoint (AEs/1000 patient-days) and other event rate secondary endpoints (e.g., number of AEs/100 admissions, preventable AEs/1000 hospital days etc.) will be based on mixed-effects Poisson regression models, entering as fixed effects the control period and a time term to account for a potential underlying trend in AE rates over the study period, and a random effect accounting for the unit level. A potential interaction term between time and intervention will be tested to identify a possible learning curve.^[5]^ Pre-specified supportive analyses will be performed to take into account possible changes in specific confounding factors over time by further adjusting for the demographic and clinical characteristics of children, including a lower term – GA at birth <28 weeks; birth weight <1000 g; length of hospital stay.^[9,19,25]^ Treatment-effect heterogeneity across clusters and varying secular trends across clusters will also be investigated by introducing the intervention and time terms as random slopes, respectively.^[51]^

The analysis of binary secondary endpoints will be based on mixed-effects logistic regression models, following similar modelling principles such as those previously described for the primary endpoint.

The descriptive analysis results will be presented as number (%) for categorical data or mean (standard deviation) or median (interquartile range) for continuous variables, depending on the characteristics of the observed distributions. Univariate comparisons between periods will rely on Student's *t* test for paired series or Wilcoxon signed ranks for quantitative variables, depending on the application conditions.

All missing or invalid data will be systematically checked and searched for in patients’ medical records. For multivariate analysis of the primary endpoint adjusting for potentially missing confounders, in addition to complete case analysis, a sensitivity analysis will be led using multiple imputation by chained equations to check the robustness of the findings

All analyses will be performed with Stata v16.0 (StataCorp, College Station, TX, USA).

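### Paired t and Wilcoxon signed-rank tests between periods have almost no valid infant pairs, and unit-level pairs would leave calendar time unadjusted for quantitative variables

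*Protocol article*

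**What the plan says.** In the protocol article, section 2.8.2 (Statistical analysis), the paragraph on descriptive results ends: "Univariate comparisons between periods will rely on Student's" *t* "test for paired series or Wilcoxon signed ranks for quantitative variables, depending on the application conditions". The pair is not defined.

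The same section opens by naming "the need to monitor underlying temporal trends" as one of the challenges of a stepped wedge. It assigns the primary endpoint and the other event rates to mixed-effects Poisson models with a time term and a unit random effect. Binary secondary endpoints go to mixed-effects logistic models built on similar principles. No model is named for quantitative variables.

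The design facts that bear on pairing are these:

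- Figure 1 caption: "The trial lasts 20 months (M) per participating unit"; "Each randomization cluster (C) C1, C2 and C3 comprises 4 units".
- Section 2.4: "Time blocks of 4 months will be considered".
- Section 2.8.1: "Considering a total number of 12 units divided into 3 randomization clusters over 5 study periods", with an expected mean stay of 17 to 20 days.
- Figure 1 caption, on the 4-month transition: "During this *transition* period the unit is not in a *control* or *intervention* phase".
- Section 2.8.3: 15 files per unit are drawn at random for each of the 20 months.

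**The concern.** A paired test needs the same observational unit measured under both conditions. Two units are possible here, and each has a problem.

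- **Infants.** The control and intervention periods contain almost entirely different infants. A paired test on infant-level values has nothing to pair, and any matching imposed to make it run would be arbitrary.
- **Units.** Each of the 12 units does contribute to both periods, so unit summaries can be paired. But intervention always follows control within a unit, and the paired difference has no time term. It also discards what a stepped wedge offers to separate effect from trend: the comparison, at the same time point, of units already trained with units not yet trained.

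At stake is any p-value attached to a quantitative variable. It would rest either on an invalid pairing or on a contrast that cannot tell the intervention from the passage of time.

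**Working it through.** The article gives no figure on this point to reproduce. Two checks follow, then an illustration.

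**1. Timeline within a unit.** Inputs: 20 months per unit, five blocks of 4 months, a one-block transition, three sequences. Figure 1 is not shown, so the layout is derived from the text. Three staggered one-block transitions that leave every unit at least one control and one intervention block must fall in blocks 2, 3 and 4.

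Let *a* be the number of control blocks (1, 2 or 3). Control runs from 0 to 4*a* months, transition from 4*a* to 4*a* + 4, and intervention from 4*a* + 4 to 20.

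| Sequence | Control (months) | Intervention (months) | Gap | Midpoints | Distance |
|---|---|---|---|---|---|
| *a* = 1 | 0–4 | 8–20 | 4 | 2 and 14 | 12 |
| *a* = 2 | 0–8 | 12–20 | 4 | 4 and 16 | 12 |
| *a* = 3 | 0–12 | 16–20 | 4 | 6 and 18 | 12 |

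In general, the midpoint distance is (4*a* + 4 + 20)/2 − 2*a* = 12 months, whatever *a* is. The gap from the end of control to the start of intervention is 4 months.

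**2. Can infants be pairs?** To have days in both periods, one stay must span the whole transition: 4 × 365.25/12 ≈ 122 days. The article gives only the mean stay, so the shape of the distribution is an assumption. Readmissions are ignored, because the article gives no figure for them.

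- Exponential: exp(−122/17) = 0.08%; exp(−122/20) = 0.22%.
- Lognormal, coefficient of variation 1: 0.27% (mean 17) and 0.48% (mean 20).
- Lognormal, coefficient of variation 1.5: 0.92% (mean 17) and 1.36% (mean 20).

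So between about 0.1% and 1.4% of infants could appear in both periods. The monthly random draw lowers the share further in the chart-review sample. The length-of-stay argument also holds for the full study population.

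**3. What if the 12 units are the pairs?** Suppose the variable has a linear trend of *b* per month and the intervention effect is θ. The expected paired difference is θ + 12*b* in every sequence. Since the multiplier is the same in all three, averaging over the 12 units cancels nothing. As an assumed range, a trend of 0.5% to 1% of the mean per month gives 12 × 0.5% = 6% to 12 × 1% = 12% added to, or hidden in, the difference.

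**4. Illustration of the error rate.** The mechanism was simulated with 1,000 runs: no intervention effect, 12 units, 60 infants per unit and block, mean stay 18.5 days, a base of 60 events per 1000 patient-days, and a between-unit SD of 0.2 on the log scale. The drift and the SD are assumptions. The unit-paired *t* test at nominal 5% rejected in:

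- 5.9% of runs with no drift;
- 7.5% at −2% per year;
- 19% at −5% per year;
- 63% at −10% per year.

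The simulated outcome is an event rate, which the plan does not analyse with a paired test. The figures show how an untreated trend acts on a unit-paired test. They are not an estimate for any endpoint of this trial.

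**The case against.** The strongest reply is that the sentence closes a descriptive paragraph and governs no effectiveness rate. The Introduction describes each cluster as its own control, and randomisation is at unit level, so pairing the 12 unit summaries is a legitimate reading. A condensed article may leave the unit of analysis to the full protocol. If the purpose is to show whether case mix (gestational age, birth weight, length of stay) differs between periods for any reason, calendar time included, then an unadjusted difference is the quantity wanted and not a biased effect.

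Much of this stands. It limits the point to quantitative variables and makes the right replacement depend on purpose. It does not rescue the sentence. The article names a paired method, so this is not merely missing detail. For infant-level case mix, the suitable comparison is unpaired with clustering by unit. For a quantitative outcome used to judge the intervention, the unit-paired version conflicts with the section's own insistence on temporal trends.

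Three stronger readings are tempting, and the article does not support them:

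- A reader might set the 6% to 12% drift against the 17% target reduction in section 2.8.1 and infer a threat to the primary result. That target is an adverse-event rate, analysed with a time-adjusted Poisson model and not with these tests.
- A reader might take 12 months as the gap between periods. It is the distance between midpoints; the gap is 4 months.
- A reader might infer that the economic or health-outcome endpoints of section 2.6.2 will be tested this way, or that these p-values will be printed beside the model results. The article says neither. It only names no other inferential method for quantitative variables.

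The dermatitis score before and after antiseptic use (section 2.6.2) can be paired within an infant, but the sentence concerns comparisons between periods.

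**Conclusion.** The point holds for quantitative variables only. On infant data the named tests have no valid pairing: under the assumed stay distributions, at most about 1.4% of infants could contribute to both periods. On the 12 unit summaries they are a before-after contrast that carries 12 months of any secular trend in every sequence. How large that is depends on a trend the article does not give; 6% to 12% of the mean corresponds to an assumed 0.5% to 1% per month, and with no trend the bias is nil. The 12-month figure rests on a layout derived from the text, though it holds for any position of a single one-block transition within the five blocks.

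The primary endpoint, the other event rates and the binary endpoints are untouched. This is worth correcting because the stated method is unsuitable and cheap to replace, not because the main conclusion depends on it.

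**What to change.** In section 2.8.2, remove the paired *t* and signed-rank tests for comparisons between periods, and separate two uses:

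- **Quantitative outcomes used to judge the intervention:** a linear mixed model (outcome transformed if skewed) with a unit random effect, a time term and the intervention term, as in the primary model.
- **Patient characteristics:** report them by period descriptively. If they are to be tested for case-mix differences, use a method that treats infants as unpaired and clustered within units, and say that the purpose is description.

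If paired tests were meant for measures that really are repeated in the same infant, such as the dermatitis score, limit the sentence to those. The cost is analysis wording only; no data collection, sample size or primary analysis changes.

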#### Outcomes measured

2.8.3

The effectiveness of the intervention will be measured by RCR of files selected by drawing lots. As previously mentioned, this analysis will involve using the NICU trigger tool developed and described by Paul Sharek.^[42,47]^ Fifteen files/month/unit will be drawn at random from the pool of all patient files included in the study, for each of the 20 months of participation. Only the part of the file corresponding to the stay in the unit participating in SEPREVEN will be considered. AEs will be assigned to the control or intervention period according to their date of occurrence.

The records will be analyzed by reviewers external to the unit and to the promotor, educated in the RCR for the study purpose. The reviewers will be unaware of the study intervention and clusters. The analysis will be made progressively in alphabetical order of identification code, thus mixing files from the different periods. To limit internal incoherence in analysis, the same reviewer will analyze all charts from a same unit. Each suspected AE will have to be confirmed by a physician educated in the RCR and unaware of the patients’ dates of stay, in agreement with the external reviewer. In the event of disagreement between the reviewer and the physician about the presence, name, severity or preventability of the AE, the case will be discussed with a third physician and consensus will be sought.

Once validated, the trigger-tool data and AE data will be entered in the e-CRF.

### Ethics, trial management and dissemination

2.9

Trial registration: NCT, registration number NCT 02598609, registered November 6, 2015.

https://clinicaltrials.gov/ct2/show/NCT02598609

The SEPREVEN study was approved by the National Data Protection Authority (CNIL no 915263) and the ethics committees (Consultative Committee on the Treatment of Data on Personal Health for research Purposes, France CCTIRS no 15327) and Committee for the Protection of People Participating in Biomedical Research CPP Ile-de-France III, France (no ID RCB: 2014-A01751-46).

A four-letter number will be automatically generated when a new patient is entered on the e-CRF. A correspondence sheet containing this number and the patient's identity (surname, first name, date of birth) will be completed by the research assistant of each unit. At the e-CRF level, all data will be anonymized. The data recorded during this research will be processed electronically in accordance with Act No. 78-17 of 6 January 1978 on data processing, files and liberties, as amended.

Finally, as part of the study, each unit's team will sign a commitment to respect a specific Caregiver Protection Charter, which implies the requirement of non-punitiveness of HCPs associated with error reporting in the study.

Protocol contributors: LC conceptualised the study, EA conceptualised the design and analysis. CJ is responsible for the project administration.

The results will be published in peer-reviewed journals and disseminated through presentation at scientific conferences. Authors will be professionals participating in the research.

### Protocol amendments

2.12

The research will be conducted in accordance with this protocol. Protocol amendments with substantial changes in the protocol have been tracked and dated. Up to January 2020, 4 amendments have been submitted and have been accepted by the Committee for the Protection of People Participating in Biomedical Research CPP Ile-de-France III - no ID RCB: 2014-A01751-46). Content of substantial changes and regulatory authorities agreement are available as a supplementary file.

### Patient and public involvement statement

2.13

Patient representatives (Association SOS Prema, France) were not involved in the protocol design, but will be partners of the research in the reporting of the results and outcomes and in the dissemination plans. They will also be involved in the study on communication of errors with parents.

### Monitoring

2.14

In the first months of the study, a monitoring will cover at least 10 files per unit and will concern all data to be entered for these files. Additional monitoring will be carried out on the units for which anomalies have been identified as well as for all the patients who died. Another specific monitoring will concern AE collection (date, type, severity).

A global monitoring will be generated over time automatically from the eCRF-level to complete or correct missing or irrelevant data and sent to the units until correction is made. LOS data will be monitored by comparing the data of each unit with those of its annual institutional report of bacteriaemia. Regarding implementation of the intervention, there will be no direct audit procedure, but an independent company is responsible for the RCA-like educational program in the units. For the second part of the intervention (bundles) the principal investigator (LC) and the local investigator will work together in order to create, print and implement the bundles.

Regarding the data from the trigger tool RCR, all the charts will be analyzed by professionals from another independent company and checked by a clinician.

## Discussion

3

Patient safety is a key issue that concerns everyone using the healthcare system but also carers, policy makers, health economists, and the whole society. Despite this, at this stage, the rate of AEs does not seem to be controllable, and studies measuring the efficiency of standardized prevention programs are lacking. In comparison with studies of other health-related causes of death, studies improving knowledge in this field are rare. As commented by Peerally et al, RCA presents a number of flaws – like susceptibility to political hijack, tendency to produce poor risk controls, poorly functioning feedback loops, failure to aggregate learning across incidents and confusion about blame and responsibility.^[36,37,40]^ Innovative context-related research strategies are needed to identify preventable AEs, related severity of outcomes as well as a reliable measure of the efficiency of strategies to improve safety.^[2]^

Typically, AEs are types of injuries that most frequently are due to an error in treatment rather than the underlying condition of the patient. However, in clinical practice, preventability definition is not consensual because of a degree of subjectivity and context-dependent causalities.^[48,52]^ A systematic review in 2012 concluded no available definition of preventability; the most common definition used in studies was the presence of an identifiable and modifiable cause of harm, completed with the concept of a failure to act according to “available knowledge” or to follow “accepted practices” on a system or individual basis.^[48]^ Some authors have proposed to create an internationally accepted definition of preventable AEs to increase the reproducibility of RCRs and the identification of ME-related injuries.^[53]^

Our study will generate knowledge in the field of patient security by targeting 2 dimensions: first, it will assess the efficiency of an educational program combining prevention of nosocomial infections and a type of RCA targeting also other types of AE, in a NICU micro-environment. Second, it will offer a prospective aggregate description of MEs’ characteristics in NICU patients as well as the damage they caused at the multi-institutional level. The grading of severity will help identify the AEs most involved in patients’ altered security. Hence, our project combines actions related to patient safety in its various components. Finally, our data will raise some original ethical issues around the disclosure of MEs to families and on the proxy's role as a co-actor in patient safety.
